### Standard of Care (Easy Call System)

Easy Call is the standard of care in the Ajmera Transplant Program within the UHN. This system allows transplant health care providers to leave messages for the patients regarding changes in their medication and appointment reminders. Patients, in turn, can also leave messages for health care providers should they require further clarification on their care. The Easy Call system will be available to both arms of this study.

### Outcomes

The primary outcome for this study will be any unscheduled hospital admission or ED and unscheduled transplant clinic visit post discharge from the index admission during which the patients received their organ transplant. Readmissions and unscheduled ED/transplant clinic visits will be captured at 30 days, 3 months, and 1 year after organ transplant. A Central Adjudication Committee (CAC) composed of two transplant physicians from each organ group (ie, heart, kidney, and liver) will review each reported readmission to determine if they are study events and the most responsible diagnosis for readmission. Secondary outcomes will be assessed to capture participant illness experience and further quantify between-group differences in recovery from index transplantation. These will include patient-reported outcomes using validated self-administered questionnaires (see next section), 1-year graft survival rate, 1-year patient survival rate, number of Easy Call interactions, and index length of stay compared to pretransplant activity level (ie, step count). The CAC will also review all reported secondary outcomes and cases of graft loss or patient death to adjudicate the cause. Any disagreements within the CAC will be resolved by consensus.

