### Screening and Recruitment

Patients on the UHN transplant waiting list will be screened by study personnel for participation in this study. Consent and enrollment will be completed while participants are still on the transplant waiting list. Prior to discharge from the index hospitalization, patients will be randomized to either the intervention or control group. All patients will be given an Apple Watch at the time of discharge from their index hospitalization to record continuous ambulatory physiologic data. The use of smartwatch technology will allow autonomous step count tracking and rapid clinician intervention in response to patient inactivity, heart rate monitoring, heart rate variability, intermittent electrocardiography, and the development of robust ambulatory physiologic data that can power predictive ML algorithms for adverse patient outcomes.

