### Study Follow-up

All participants will be followed at set intervals (approximately 30 days, 3 months, and 1 year from transplant), with participant health status and outcomes recorded at each point. A 1-year follow-up period was chosen as the study period as most patient challenges occur in the first year following transplant [8]. This time frame is the period of maximal benefit to patients and care providers when we anticipate the majority of unplanned but potentially avoidable readmission occurring.

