### Statistics

Currently at the UHN, approximately 20% of patients are readmitted to the hospital within 30 days post SOT. In general, these patients are readmitted following presentation to either the ambulatory transplant clinic or ED. Although we do not have data on the number of patients that present to the ambulatory transplant clinic within 30 days post SOT, previous work has shown ED visits at 30 days to vary greatly between SOT groups (eg, as low as 17% for patients with kidney transplants, and as high as 44% for patients with liver transplants) [24,25]. Given this variability, we hypothesized a conservative estimate of 20% for our 30-day composite end point. To observe a 50% relative risk reduction, from 20% to 10%, for the 30-day composite end point, at an alpha of .05 and power of 0.8, 199 participants will need to be recruited for each group.

We will evaluate all outcomes using the intention-to-treat analytical approach. A Cox proportional hazard model will be used to evaluate the effect of the mHealth app on posttransplant unplanned readmission and ED and unscheduled transplant clinic visit rates (primary outcome). Results of this analysis will be reported as hazard ratios with 95% CIs. Kaplan-Meier curves will be used to depict freedom from unplanned readmission. Subsequent to running the Cox proportional hazard model, a logistic regression model will be used to analyze unplanned readmission rates at the prespecified time points of 30 days, 3 months, and 1 year. Results of the logistic regression model will be reported using odds ratios and 95% CIs.

Generalized linear models to estimate the mean difference in the intervention compared to the control group will be used to estimate the impact of personalized communication through the mHealth app on posttransplant patient-reported outcomes (secondary outcomes).

To avoid spuriously inflated estimates of treatment effect, an interim analysis will be conducted when 50% of participants are enrolled and have completed follow-up. The results of this analysis will be reviewed by an independent data monitoring committee. The O’Brien-Fleming stopping rule will be used based on our primary outcome and requires a *P*≤.007 [26]. This conservative rule will avoid premature trial termination unless a large treatment effect is observed.

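### The primary event can occur only after index discharge, but its 30-day, 3-month and 1-year points are counted from transplant, so exposure in the 30-day analysis depends on length of stay

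*Protocol article*

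**What the plan says.** **Event.** The Outcomes section of the protocol article defines the primary outcome as an unscheduled admission, emergency department visit or unscheduled transplant clinic visit "post discharge from the index admission during which the patients received their organ transplant".

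**Clock.** The next sentence there reads "Readmissions and unscheduled ED/transplant clinic visits will be captured at 30 days, 3 months, and 1 year after organ transplant". Study Follow-up uses the same origin: participants are "followed at set intervals (approximately 30 days, 3 months, and 1 year from transplant".

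**Randomization.** Under Screening and Recruitment: "Prior to discharge from the index hospitalization, patients will be randomized to either the intervention or control group". No fixed day after transplant is given.

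**Planning and analysis.** Statistics starts from the centre's own experience that "approximately 20% of patients are readmitted to the hospital within 30 days post SOT". It sizes the trial to detect a fall "from 20% to 10%, for the 30-day composite end point, at an alpha of .05 and power of 0.8", and concludes that "199 participants will need to be recruited for each group". A Cox model is the first analysis of the primary outcome. A logistic model then serves to "analyze unplanned readmission rates at the prespecified time points of 30 days, 3 months, and 1 year". All outcomes are analysed by intention to treat.

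The article does not restart the clock at discharge or randomization, and it does not give the time origin of the Cox model.

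**The concern.** The event definition and the clock start at different moments. A patient cannot have a primary event while still in the index admission, yet those inpatient days use up the 30-day window. Two patients with the same risk at home can therefore have very different chances of an event by day 30, only because one went home sooner. Stays can be expected to differ among heart, kidney and liver recipients, and the protocol treats index length of stay as variable enough to relate it to pretransplant activity as a secondary outcome.

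A Cox model started at discharge or randomization would handle this. A binary analysis at day 30 makes no allowance for unequal exposure.

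Two things are at stake. The 30-day proportion mixes the risk of returning to hospital with the length of the first stay. In addition, an event in a patient's first month at home that falls after day 30 from transplant is missing from the 30-day result, although the app is meant to act in that period.

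**Working it through.** **1. Reproduce the plan's figure.** Inputs from Statistics: 20% against 10%, alpha 0.05 (taken as two-sided), power 0.80. Two proportions, pooled variance, no continuity correction, mean proportion 0.15:

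n = [1.960 × √(2 × 0.15 × 0.85) + 0.842 × √(0.20 × 0.80 + 0.10 × 0.90)]² / 0.10²
= (0.990 + 0.421)² / 0.01 ≈ 199 per group.

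This matches the protocol exactly. Power at 199 per group is 0.800.

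**2. Time at risk in each window.** From the two definitions, days at risk = max(0, window − length of stay). Length of stay is not in the documents, so the stays below are assumptions. Windows are 30, 91 and 365 days.

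| Assumed stay (days) | Days at risk by day 30 | Share of 30 days | Share of 3 months | Share of 1 year |
|---|---|---|---|---|
| 7 | 23 | 77% | 92% | 98% |
| 14 | 16 | 53% | 85% | 96% |
| 21 | 9 | 30% | 77% | 94% |
| 30 | 0 | 0% | 67% | 92% |

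The mismatch is large at 30 days, moderate at 3 months and small at 1 year.

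**3. Patients still in hospital at or near day 30.** Such a patient, once randomized, has little or no time at risk. The article gives no rule for this case. Under intention to treat the patient would presumably enter the 30-day logistic model as a non-event. That is an inference.

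**4. What it could mean for event rates (illustration only).** Assume a constant hazard and one common stay L for everyone.

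*Reading A: the 20% is a from-transplant figure, as Statistics words it.* The planning rate and the endpoint then share a clock, and 199 per group gives its planned 80% power. A 30-day window opened at discharge would see 1 − 0.8^(30/(30 − L)) in controls and 1 − 0.9^(30/(30 − L)) in the intervention group:

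| L (days) | Control | Intervention | Power at 199 per group |
|---|---|---|---|
| 5 | 23.5% | 11.9% | 0.86 |
| 10 | 28.4% | 14.6% | 0.92 |
| 15 | 36.0% | 19.0% | 0.97 |

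*Reading B: the 20% is really a risk over 30 full days at home.* The from-transplant window would then see 1 − 0.8^((30 − L)/30) against 1 − 0.9^((30 − L)/30):

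| L (days) | Control | Intervention | Power at 199 per group |
|---|---|---|---|
| 5 | 17.0% | 8.4% | 0.73 |
| 10 | 13.8% | 6.8% | 0.64 |
| 15 | 10.6% | 5.1% | 0.52 |

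Reading A follows the protocol's wording; Reading B goes against it. Together they show how much the choice of clock can move the 30-day rate. They do not estimate the trial's actual power.

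**The case against.** **The three time points may be a visit schedule.** Outcomes are recorded at approximate intervals, the Cox model comes first, and its time origin is a detail that an article can leave to the full protocol or analysis plan. The part about the Cox model stands: a missing origin is not an error in itself. The rest does not, because the logistic analysis uses these same points as analysis times, the sample size is built on a 30-day composite, and the only origin the article states for them is transplant.

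**The sample size agrees with its own clock.** This stands. A reader might infer from Reading B that the trial is underpowered. The documents do not support that, since the 20% is itself counted from transplant.

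**The arms are treated alike.** This also stands. Randomization comes at the end of the index stay, so length of stay is almost wholly settled beforehand, both arms share the clock, and organ is a stratification factor. A reader might infer a biased comparison; none follows.

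**Nothing says that long-stay patients are scored as successes.** Correct. No rule is shown, and a patient still in hospital at day 30 may not yet be randomized.

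**Moving every time point to discharge would disturb the questionnaires.** EQ-5D and PROMIS are timed from transplant, and there is no reason to move them. A discharge origin also gives no start time to someone who is randomized and dies before discharge. Both points limit the fix.

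**Conclusion.** The point holds in a limited form. The event starts at discharge and the clock at transplant, and both are stated rules. In the 30-day analysis, exposure is therefore 30 days minus the index stay. It varies by patient, very probably by organ, and can fall to zero. This blurs the 30-day endpoint and drops some first-month-at-home events. A 14-day stay removes 47% of the 30-day window but about 4% of the 1-year window.

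It does not bias the arm comparison, it does not invalidate 199 per group, and no shortfall from the planned 80% power is shown. The treatment of patients still in hospital at day 30 is inferred from the intention-to-treat statement. All rates and power values beyond the protocol's own rest on assumed stays, a constant hazard and one common stay for everyone. The change is worth making because it is cheap and concerns the time point on which the trial was sized.

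**What to change.** For the primary outcome only:

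- Use one time origin for both the Cox model and the 30-day, 3-month and 1-year logistic windows. Either randomization, carried out at index discharge, or index discharge itself would serve. Amend Outcomes and Statistics to say so.
- State how a death between randomization and discharge is handled.
- In Study Follow-up, keep the visit and questionnaire schedule timed from transplant, and add that the primary-outcome windows run on their own clock.
- State that the 20% planning rate is a from-transplant readmission figure, and check it on the new clock where centre data exist. That is possible for readmissions. It is not possible for clinic visits, because Statistics says that the centre has no data on clinic presentations in the first 30 days.

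The cost is protocol and database wording, plus primary-outcome follow-up that ends later by the length of the index stay.

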### Patient-Reported Outcomes

A health outcomes questionnaire (EQ-5D) and the Patient-Reported Outcomes Measurement Information System (PROMIS) Global Health Scale will be used to assess patient-reported outcomes. The EQ-5D is a comprehensive, compact health status classification and health state preference system. This questionnaire is widely used and has demonstrated validity and sensitivity in many populations [13-15]. PROMIS is a set of person-centered measures that evaluates and monitors physical, mental, and social health in adults and children. It can be used with the general population and individuals living with chronic conditions [16,17]. Both the EQ-5D and PROMIS questionnaires will be completed by participants at minimum 30 days, 3 months, and 1 year after SOT.

### Study Follow-up

All participants will be followed at set intervals (approximately 30 days, 3 months, and 1 year from transplant), with participant health status and outcomes recorded at each point. A 1-year follow-up period was chosen as the study period as most patient challenges occur in the first year following transplant [8]. This time frame is the period of maximal benefit to patients and care providers when we anticipate the majority of unplanned but potentially avoidable readmission occurring.

### ML Approach

Clinical and physiologic data captured in phase one will be continuously streamed from the Reboot 2.0 mHealth app on each participant’s smartphone to Pattern Health’s centralized secure server hosted by Amazon Web Services in the United States. This centralized data lake will be used to develop ML algorithms in the second phase of the study to better interpret raw patient data. Phase one data will consist of routine clinical data taken at baseline and regular follow-up appointments including demographics, comorbidities (eg, chronic kidney disease, diabetes, hypertension, obesity, and longitudinal changes in weight over time), metabolic scale body measurements, and laboratory and imaging investigations; ambulatory physiologic data collected via the Apple Watch (eg, vital signs and activity level); and laboratory and test results entered into the mHealth app (eg, blood glucose measurement or insulin administration). Additionally, details regarding the immunosuppression regimen used and longitudinal changes made will be incorporated. Some episodes of rejection, particularly in patients with liver transplants, may be managed as an outpatient, resulting in modifications to the immunosuppression regimen over time. Medications used for treatment of comorbidities (eg, diabetes, hypertension, or viral hepatitis) will also be taken into consideration (see Multimedia Appendix 1). These data will be automatically streamed into the centralized data lake (in the case of Apple Watch and patient-reported data) or extracted from the participant’s medical record.

Categorical measurements (eg, gender) will be one-hot encoded [18] prior to normalization and temporal adjustment. Specifically, all participant demographic variables will be independently normalized to have mean zero and SD of one. Each feature with missing values will have a corresponding binary variable added denoting if the variable was observed or not. EQ-5D data will be coded into the five dimensions of health as five distinct features for analysis and following established guidelines for normalization [19]. The PROMIS Global Health scale will be coded using a similar approach. All other variables will be independently normalized to have a mean of 0 and an SD of 1. Measurement of mean, SD, maximum, and minimums will be recorded over fixed intervals, and the number of most recent intervals precluding an event will be included in the model (eg, the average heart rate per 3-day window taken over 12 days yields 4 distinct measurements). Missing measurements will be counted per interval as an additional feature. For each patient window, this will create a fixed length feature variable that can be directly included and compared across the statistical and ML models. The interval width and number of intervals will be determined experimentally within the training data set. Following data processing, self-normalizing neural network [20], long short-term memory [21], random forest model [22], and extreme gradient boosted decision tree [23] approaches will be applied on a training portion of the data set to assess risk factors for the development of transplant outcomes. Early ML models will support the development of a ranked features list of clinically relevant variables, which will be used to inform subsequent model development.

The accuracy of each model (discrimination and calibration) and their relative performance (net-reclassification index) will be assessed in a portion of the data set reserved for testing. The development of predictive ML algorithms for adverse patient outcomes will allow for future personalized posttransplant medicine and early clinical intervention based on patient-specific data.

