## Methods

### Overview

Remote Mobile Outpatient Monitoring in Transplant (Reboot) 2.0 is a registered (ClinicalTrials.gov NCT04721288) two-phased single-center study. It has also been approved by the University Health Network (UHN) Research Ethics Board (REB 20-6082.0.1). The first phase will consist of a 1-year concealed randomized controlled trial of 400 adult SOT (heart, kidney, or liver) recipients. Currently, the Ajmera Transplant Centre at the UHN (a large academic teaching site in Toronto, Canada) uses paper medical administration records to alter immunosuppressive medications, and patients generally record their vitals by pen and paper, both of which may be error prone. Additionally, health care providers and patients with transplants rely on a telephone-based (“Easy Call”) method of communication, wherein patients leave a message for their health provider when issues arise. The integration of medication and vitals tracking, as well as patient-provider communication into a single mHealth app may decrease errors and improve patient outcomes. To test this, participants will be randomized to receive either personalized communication using an mHealth app in addition to the Easy Call system (intervention group) or Easy Call standard of care (control group; see Figure 1). In the second phase of Reboot 2.0, the data set from the 400 patients with SOTs collected as part of phase one will be evaluated in an attempt to identify early markers of rejection, infection, and graft dysfunction posttransplant.

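### Phase-two predictors are taken from the intervals just before the event, with no lead gap stated, so test-set accuracy from this design does not demonstrate early prediction

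*Protocol article*

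**What the plan says.** The Overview gives the aim of phase two as an attempt to "identify early markers of rejection, infection, and graft dysfunction posttransplant". The Introduction adds the hypothesis that machine learning will predict adverse outcomes more accurately than conventional regression.

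The ML Approach section describes the predictors. Measurements are summarised over fixed intervals, and "the number of most recent intervals precluding an event will be included in the model". The example is that "the average heart rate per 3-day window taken over 12 days yields 4 distinct measurements". What will be tuned is limited: "The interval width and number of intervals will be determined experimentally within the training data set". The unit is a window: "For each patient window, this will create a fixed length feature variable", which is fed to the statistical and the machine learning models alike. In addition, "Missing measurements will be counted per interval as an additional feature". Discrimination, calibration and net reclassification are then assessed in a reserved test portion.

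Under Screening and Recruitment, "All patients will be given an Apple Watch at the time of discharge from their index hospitalization", so wearable data begin at discharge.

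**The concern.** Counting windows back from the event lets the outcome choose the sampling time of its own predictors. Three things follow.

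1. **The features cannot be formed in use.** A clinic that wants a warning does not know the event date and so cannot pick the intervals leading up to it.
2. **The last interval touches the event.** With no gap stated, it can contain the illness that brought the patient in. A model may then score well by recognising the presentation, not by anticipating it.
3. **Patients without an event have no date to count back from.** If their windows fall later after transplant than the event windows do, anything that changes with recovery separates the two groups without predicting anything. Missing counts can do the same, because a window that reaches back before discharge has no watch data.

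The test portion would be built by the same rule, so none of the planned performance measures would reveal this. At stake is the main claim of phase two, that the models support early intervention.

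**Working it through.** **The plan's own figure.** The article gives no performance target or sample size for phase two. The only figure on this point is the window example, and it is consistent: 12 days / 3 days = 4 intervals. Counted back from the event they cover days 12-9, 9-6, 6-3 and 3-0. The oldest has about nine days of lead and the newest has none.

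**What is fixed and what is open.** The event anchor is stated. Interval width and number are to be tuned. The anchor, the prediction horizon and the lead gap are not among the tuned items, so tuning does not remove points 1 and 2.

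**Point 3: inputs.** The document supplies 400 patients, one year of follow-up and watch data from discharge. It gives no timing for rejection, infection, graft dysfunction or death, so the rest is assumed. Event times are Weibull with cumulative hazard λu^k, where u is the fraction of the year and λ = −ln(1−q) for one-year risk q. Shape k = 1 is a constant hazard; k = 0.7 and 0.5 are moderately and strongly front-loaded.

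**(a) Time since discharge alone, no physiologic signal.** Let G(u) = [1 − exp(−λu^k)]/q be the distribution of event times among patients with an event. If event-free windows end on a random day, AUC = ∫G(u)du from 0 to 1. Example with q = 0.20, k = 1: λ = 0.2231, and AUC = [1 − 0.20/0.2231]/0.20 = 0.1037/0.20 = 0.52. For q from 10% to 40%:

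| Event-free windows end | k = 1.0 | k = 0.7 | k = 0.5 |
|---|---|---|---|
| time-matched to events | 0.50 | 0.50 | 0.50 |
| random day | 0.51-0.55 | 0.60-0.63 | 0.67-0.71 |
| at one year | 1.00 | 1.00 | 1.00 |

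The last row is true by construction. Time since discharge is not named as an input in the article's text, so in practice it would act through proxies.

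**(b) A proxy: a step-count-like marker with no effect on risk.** Marker = 1 − exp(−t/τ) + b, with τ = 30 to 120 days and b normal between patients with SD 0.3 of full recovery (assumed); 400 patients, 350 days after discharge, q = 30%:

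| Event-free windows end | k = 1.0 | k = 0.7 | k = 0.5 |
|---|---|---|---|
| time-matched to events | 0.50 | 0.50 | 0.50 |
| random day | 0.51-0.52 | 0.56-0.58 | 0.63-0.65 |
| end of follow-up | 0.58-0.72 | 0.63-0.77 | 0.68-0.82 |

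Taking q from 20% to 50% moves the entries by no more than about 0.03, which gives overall ranges of about 0.51-0.66 and 0.57-0.82. A wider spread between patients shrinks the effect: with SD 0.5 and q = 30%, the k = 0.5 column falls to 0.60-0.61 and 0.64-0.73.

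**(c) Incomplete windows.** The share of first-year events within 12 days of discharge is G(12/365). Example with q = 0.20, k = 0.5: 1 − exp(−0.2231 × √(12/365)) = 1 − exp(−0.0405) = 0.0397, and 0.0397/0.20 = 20%. Over q = 10% to 40% and k = 0.5 to 1.0 the share is 4% to 22%. Those events lack a full 12-day window, and their missing counts reflect recent discharge.

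**The case against.** The strongest reply is that this is a condensed article. The rule for event-free windows may stand in a fuller plan, and the text mentions a temporal adjustment and speaks of each patient window, which would fit several windows per patient, event-free ones included. This stands as far as point 3 is concerned. A reader might infer that the models will score well from time since discharge alone, and the document does not support that: the size runs from nothing to large according to a rule it does not state. The reply does not reach points 1 and 2, because the event anchor is written down and neither phrase removes it.

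A reader might also infer that early markers cannot be found at all. That goes too far. The older intervals enter as separate features, and their number and width are open.

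Nor is every gain from time an artefact. If risk truly falls after discharge, being recently discharged is genuine prognostic information. With pooled weekly prediction times and a day 3-14 horizon under a falling hazard, the same risk-free marker still scores about 0.53 to 0.58. An AUC of 0.50 is therefore not the right benchmark for the repaired design.

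It is tempting to say that most early events lack a full window: 12/(30 − stay) gives 52% to 75% for index stays of 14 days down to 7 in reverse order, that is 52% for 7 days and 75% for 14. Those stays are assumed, and the figure covers only 30-day events spread evenly. It does not describe first-year events.

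Finally, regression and machine learning receive the same features, so nothing here shows that the comparison between them is tilted.

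**Conclusion.** The point holds for what the text fixes. Predictors anchored on the event, with no lead gap stated, cannot be formed in use and may contain the presenting illness. Accuracy obtained this way does not demonstrate early prediction, and the reserved test portion cannot expose the problem. This rests only on reading 'precluding' as 'preceding'.

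The recovery-time effect is conditional. It is absent if event-free windows are time-matched, small to moderate with random days (about 0.51-0.66), and potentially large at end of follow-up (about 0.57-0.82). All these values rest on assumed event timing, recovery speed and spread between patients. The randomized comparison in phase one is not affected. The change should be made before modelling begins.

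**What to change.** Replace the event-anchored windows with prediction times common to all patients still at risk, for example weekly from discharge. At each one, use only data recorded earlier, and predict the event in a stated later horizon that starts after a lead gap, for example days 3 to 14 after the prediction time.

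Include time since discharge in every model, the regression models included. Report a benchmark model with time alone, so that any gain beyond genuine time-varying risk is visible.

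The change needs new wording and some data preparation, and no new data. Reported discrimination will look less favourable, and the earliest events will be predicted from fewer wearable data.

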In the transplant population, it is likely that remote monitoring will improve medication adherence/adjustments and will allow for identification of early decompensation and reduce preventable hospital readmissions. Thus, this study will determine if an innovative mHealth intervention designed to improve patient-clinician communication reduces unnecessary hospital readmission and visits to the emergency department (ED) and transplant clinic when used in addition to the standard of care telephone communication system. We will also incorporate clinical and continuous ambulatory physiologic data collected as part of the mHealth intervention to develop machine learning (ML) algorithms capable of identifying early indicators of adverse outcomes in adult patients with heart, kidney, and liver transplants.

Therefore, we hypothesize that the delivery of personalized communication using an mHealth app will improve patient self-management, resulting in a reasonable reduction in preventable hospital readmission and unscheduled visits to the ED and transplant clinic of 50%. With tailored communication through the mHealth app, we expect fewer standard of care phone messages for patients in the intervention group, and patients with higher activity levels (average daily step count) pretransplantation will have lower index hospitalization length of stay. Finally, the large data set collected from this study will allow novel ML-derived risk prediction models to more accurately predict adverse outcomes (eg, organ rejection, infection, and death) compared to conventional regression models.

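### The only measure named for comparing the phase-two prediction models, the net reclassification index, can favour a model that ranks patients identically and is worse calibrated

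*Protocol article*

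**What the plan says.** The Introduction of the protocol article states the phase-two hypothesis: the machine-learning models will "more accurately predict adverse outcomes (eg, organ rejection, infection, and death) compared to conventional regression models".

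The ML Approach section lists the candidates as "self-normalizing neural network [20], long short-term memory [21], random forest model [22], and extreme gradient boosted decision tree [23] approaches". It then divides the evaluation in two. Each model is assessed on its own: "The accuracy of each model (discrimination and calibration". The models are compared with one another through "their relative performance (net-reclassification index". Both parts "will be assessed in a portion of the data set reserved for testing".

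No other comparative measure is named: no difference in AUC, no difference in a proper score such as Brier or log score, and no net benefit. The article does not say whether the index is category-free or uses risk categories, and gives no cut-offs. The data are "the data set from the 400 patients with SOTs collected as part of phase one", and the share held out is not stated.

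**The concern.** The hypothesis is about accuracy, and the one comparative measure does not measure it. The net reclassification index adds two parts: among patients with the event, the share whose predicted risk goes up minus the share whose risk goes down; among patients without the event, the reverse. The category-free version ignores how far a risk moves, and neither version asks whether the new value is closer to the truth. A model that only exaggerates another model's risks adds no information and spoils its probabilities, yet it can score well.

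At stake is the phase-two comparison. A model could be reported as the better performer when it discriminates equally well and gives worse probabilities, or marked down for being slightly too cautious. The Discussion intends the algorithms for tailored care, so the probabilities themselves matter.

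**Working it through.** **The plan's own figure.** There is none for the index. The only calculation in the article, 199 per group for 20% v 10% at 30 days, belongs to phase one. It reproduces with the pooled two-sided formula for two proportions and plays no part here.

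**Assumptions.** The article gives no prevalence, predictor strength or degree of miscalibration for the prediction outcomes, so I assume:
- outcome prevalence π = 10%, 20% or 30%;
- true log-odds = a + x, with x standard normal and a chosen to give π (AUC 0.750, 0.745 and 0.742);
- reference model = the true risk p, which is perfectly calibrated;
- rival model q, with logit q = m + k(logit p − m) and m = logit π. For k > 1 the risks are stretched, for k < 1 shrunk.

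**Step 1: ranking and calibration.** q is an increasing function of p, so the AUC is the same. The calibration slope of q is 1/k: 0.80, 0.67 and 0.50 for k = 1.25, 1.5 and 2.

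**Step 2: category-free index.** For k > 1, q exceeds p exactly when p > π. Hence

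NRI = [2·P(p>π | event) − 1] + [1 − 2·P(p>π | no event)] = 2·[P(p>π | event) − P(p>π | no event)].

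This does not contain k, so a slight stretch scores as much as a gross one. By numerical integration:
- π = 10%: 2 × (0.6866 − 0.3202) = +0.73
- π = 20%: 2 × (0.6826 − 0.3245) = +0.72
- π = 30%: 2 × (0.6793 − 0.3261) = +0.71

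Simulations of the same set-up gave +0.70 to +0.73.

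**Step 3: Brier score (lower is better).**

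| Prevalence | True model | k = 1.25 | k = 1.5 | k = 2 |
|---|---|---|---|---|
| 10% | 0.0817 | 0.0825 | 0.0848 | 0.0935 |
| 20% | 0.1386 | 0.1397 | 0.1427 | 0.1523 |
| 30% | 0.1770 | 0.1782 | 0.1813 | 0.1904 |

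The copy is worse in every cell, while the category-free index favours it in every cell.

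**Step 4: fixed risk categories, same inputs.**
- One cut-off at the prevalence: 0, because no patient crosses it.
- One cut-off at 10%, 20%, 30% or 50%: 0 to +0.17.
- Two cut-offs at 10% and 20%: +0.03 to +0.18.

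**Step 5: the other direction.** With k < 1 every movement reverses, so the category-free index is −0.71 to −0.73. At π = 20% and k = 0.8 the Brier score is 0.1394 against 0.1386, barely worse, yet the index is −0.72.

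**Step 6: wider inputs.** One million simulated patients per scenario, prevalence 10-40%, AUC about 0.70-0.78, k = 1.5 to 3. The category-free index was +0.58 to +0.85 for the worse model. The categorical versions gave 0 to +0.27.

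**The case against.** **Calibration is already planned.** Discrimination and calibration are to be assessed for every model in the same test data. In the example, equal AUCs and a calibration slope of 0.50 to 0.80 would be reported beside the index, and a careful reader would see the conflict. One may also argue that the article itself equates accuracy with discrimination and calibration, so the index need not decide the hypothesis. This stands, and it limits the harm. It does not remove the point: the index remains the only measure assigned to comparing models, and the article does not say how to read a disagreement.

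**The version is not stated.** The figure of about +0.7 belongs to the category-free index. With categories the false gain is smaller and can be zero. This stands, so both ranges must be given. Leaving the version and cut-offs to a fuller document is normal for an article and is not criticised. The choice of index as the comparative measure is stated in the article itself.

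**A reader might infer a bias towards machine learning,** on the ground that flexible models fitted to few events tend to be over-confident. The document does not support this. The example fits no model; it stretches a true one by hand. Regression fitted to few events can be over-confident too, and Step 5 shows that a shrunken model is penalised just as heavily. A small illustrative simulation compared fitted models with unpenalised logistic regression by the category-free index (280 training patients, about 20% events, 10 to 40 predictors, 30 repeats, all assumed). Random forest scored −0.41 to −0.48, gradient boosting −0.02 to −0.25 and a small neural network +0.14 to +0.18. The index can mislead in either direction.

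**A reader might also infer a false-positive rate, or a threat to the trial's main conclusion.** The article names no significance test for the index and does not make it a decision rule, so no error rate can be attached. The randomised comparison and its primary outcome do not use it.

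**Conclusion.** The point holds in limited form. The one measure named for the models' relative performance is not a proper measure of accuracy, while the hypothesis it serves is about predicting more accurately. Under the assumed inputs (prevalence 10-30%, AUC about 0.74-0.75, stretch 1.25-2), a copy with identical ranking and a worse Brier score gains about +0.7 on the category-free index and 0 to about +0.18 with the fixed categories tried. The sign of the category-free result follows from the algebra for any such stretch; its size depends on the assumed predictor strength. The direction of error in practice depends on which model is the more stretched, so none is claimed. The point is minor: it concerns phase two only, and the planned calibration assessment is a partial safeguard.

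**What to change.** Replace the comparative measure in the ML Approach section. On the held-out predictions, compare models by the difference in Brier (or log) score and the difference in AUC, each with a bootstrap confidence interval. Resample patients, not windows, because one patient can contribute several windows. State that these differences are read together with the calibration already planned. Keep the net reclassification index only as a supplement, with its event and non-event parts shown separately.

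The cost is small: the same predictions are used, with no new data or patients and slightly more analysis. The downside for the investigators is that a claim of superiority for machine learning may become harder to make.
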